## Abstract

**Background:**

Despite increasing investment in suicide prevention, Australian suicide rates have increased steadily in the past decade. In response to growing evidence for multicomponent intervention models for reducing suicide, the LifeSpan model has been developed as the first multicomponent, evidence-based, system-wide approach to suicide prevention in Australia. The LifeSpan model consists of nine evidence-based strategies. These include indicated, selective and universal interventions which are delivered simultaneously to community and healthcare systems over a 2-year implementation period. This study will evaluate the effectiveness of the LifeSpan model in reducing suicide attempts and suicide deaths in four geographically defined regions in New South Wales, Australia.

**Methods:**

We outline the protocol for a stepped-wedge, cluster randomized controlled trial. Following a 6-month transition phase, the trial sites will move to the 2-year active implementation phase in 4-monthly intervals with evaluation extending a minimum of 24 months after establishment of the full active period. Analysis will be undertaken of the change attributable to the invention across the four sites. The primary outcome for the study is the rate of attempted suicide in the regions involved. Rate of suicide deaths within each site is a secondary outcome.

**Discussion:**

If proven effective, the LifeSpan model for suicide prevention could be more widely delivered in Australian communities, providing a valuable new approach to tackle rising suicide rates. LifeSpan has the potential to significantly contribute to the mental health of Australians by improving help-seeking for suicide, facilitating early detection, and improving aftercare to reduce re-attempts. The findings from this research should also contribute to the evidence base for multilevel suicide prevention programs internationally.

**Trial registration:**

Australia New Zealand Clinical Trials Register, ID: ACTRN12617000457347. Prospectively registered on 28 March 2017. https://www.anzctr.org.au/TrialSearch.aspx#&&conditionCode=&dateOfRegistrationFrom=&interventionDescription=&interventionCodeOperator=OR&primarySponsorType=&gender=&distance=&postcode=&pageSize=20&ageGroup=&recruitmentCountryOperator=OR Protocol Version: 1.0, 31 May 2019.

One of the more promising suicide prevention approaches in the past decade has been the development of multicomponent models, which deliver multiple evidence-based strategies, simultaneously, in high-risk geographic regions. This approach has emerged in recognition that no single suicide prevention strategy clearly stands above the others as an effective prevention approach at either the individual or population level [4]. Multicomponent approaches typically combine a range of preventive interventions, spanning from indicated intervention for the highest risk individuals (e.g., people who have attempted suicide) through to universal prevention efforts that apply to the wider community (e.g., reducing access to means, gatekeeper training). Through the combination of universal, selected, and indicated interventions there is increased likelihood of reaching those who are reluctant to seek help, improving early identification, and improving support to high-risk individuals during critical time points for re-attempt. Growing evidence from Europe, the USA, United Kingdom, and Japan indicates that multilevel, multimodal system approaches that target health and community settings are an effective way of reducing the rate of suicide, as compared to traditional silo approaches [7, 8].

In response to the promising evidence for multilevel interventions for reducing suicidal acts (attempts and/or deaths), the LifeSpan model was developed in 2015 [9]. LifeSpan is a large-scale, community-wide trial for suicide prevention that will be implemented in four high-priority regions in New South Wales (NSW), the most populous state of Australia. LifeSpan involves implementing nine evidence-based strategies, simultaneously, for a period of 2 years. Each site has its own local implementation team so that interventions, while maintaining core features for effectiveness, may be tailored to suit the local environment. The four sites are supported by a central implementation team and a research team based at the Black Dog Institute.

The LifeSpan project represents the first scientific trial of a complex, multilevel suicide prevention approach in Australia.

### Primary aim

(i)To examine whether the LifeSpan intervention reduces *suicide attempts* after implementation in the four regions relative to rates and temporal tends established from data covering a period from 2012 until the introduction of LifeSpan in each region

### Secondary aims

(i)To examine whether the LifeSpan intervention reduces *suicide death rates* in the four regions, relative to rates and temporal tends in the pre-intervention period(ii)To examine change in rates of *suicidal acts* (both suicide deaths and attempts) after introduction of LifeSpan in the four regions, relative to rates and temporal tends in the pre-intervention period(iii)To examine the change of rates of suicidal acts in the trial sites compared to the rest of NSW where LifeSpan is not being implemented over the period of data collection

### Primary hypothesis

(i)That the suicide attempt rate will be lowered within the intervention regions after the implementation of LifeSpan compared rates and trends established in the pre-implementation period

### Secondary hypotheses

(i)That the rate of suicidal acts will be lowered within the intervention regions after the implementation of LifeSpan compared with rates and trends established in the pre-implementation period(ii)That the LifeSpan intervention sites will achieve greater reductions in the rate of suicidal acts in the period after the full establishment of the program compared to the remainder of the State (NSW) in which LifeSpan is not being implemented

The LifeSpan research program also has other secondary and tertiary aims and hypotheses, including an examination of the cost-effectiveness of the LifeSpan model, the impact of LifeSpan on help-seeking among the community and at-risk persons, and changes in referral and treatment practices. These aims and outcomes will be described in separate protocols and publications as the data for these questions will be examined in subgroups or different samples.

All study endpoints are reviewed and verified by a research evaluation and monitoring committee.

**Fig. 1 Fig1:**
[figure not shown]
Stepped-wedge trial design including baseline, establishment, active implementation, and data collection periods

Once a cluster reaches the “active intervention” phase, they have an implementation period of 2 years in which to establish all nine strategies. By the end of this 2-year period, all nine strategies are intended to be operating simultaneously.

The stepped-wedge design was chosen for logistical, political, and economic reasons. The number of clusters required for a randomized controlled trial would have been beyond the scope of the project budget, and it would have been too resource intensive to intervene simultaneously in multiple clusters in a trial of this scale. Moreover, at the time the trial was being considered, there was increasing suicide prevention activity across Australia, which led to concerns about the ability to identify control sites where new suicide prevention activity would not confound the study outcomes. Finally, the investigators were concerned that control regions would find it unacceptable to be allocated to the control condition rather than the intervention condition and be limited in their suicide prevention activities for over 2 years.

### Participants and eligibility criteria

LifeSpan aimed to deliver interventions which were integrated in a healthcare region. Regions were defined as being one or more Local Government Areas (LGAs) which interact meaningfully and fall within the boundaries of a single Local Health District or a Primary Health Network. Lead agencies within NSW were invited to submit a written application as part of an Expression of Interest (EOI) selection process. Lead agencies could be a Local Health District, Primary Health Network, or non-government organization, and needed to demonstrate that they had strong relationships with other key agencies within their region in order to deliver the programs within the LifeSpan model. Applications were assessed by a panel of five individuals holding senior leadership positions in the mental health and suicide prevention sectors, including a National Mental Health Commissioner, the Director of the Mental Health Australia Board, representatives from the NSW Ministry of Health and the NSW Mental Health Commission and NSW Aboriginal Mental Health Workforce Program.

The sites were rated against the following five key selection criteria designed to demonstrate feasibility to implement LifeSpan:
Capability and capacity of the lead agency and partnership consortiumProposed model, partnerships and project planRisk management processesCommunity engagement and communication planIndicative budget to support implementation

In addition to the above inclusion criteria, sites needed to be able to yield reliable outcome data on rates of suicide attempts and suicide deaths. Accordingly, sites were required to have a minimum base population of 145,000 persons to allow for sufficient statistical power to detect a primary intervention effect. Archival data on suicide mortality and non-fatal hospital admissions for intentional self-harm were analyzed in a preceding early phase scoping study [10] to allocate LGA geographies into quartiles for suicide mortality and morbidity indicators. LGAs with incidence rates that fell within the top quartile for suicide mortality and/or non-fatal incidents were prioritized for site selection in addition to the EOI inclusion criteria, to ensure that the LifeSpan intervention would be implemented in areas with greatest need for suicide prevention efforts. The following sites were selected as a result of this process (Table 1).

**Table 1 Tab1:** Trial sites selected to receive the LifeSpan intervention

Site (Local Government Areas within scope)	Lead agency	Site start order
“Newcastle” (Newcastle)	Hunter New England Local Health District	1
“Illawarra Shoalhaven” (Wollongong, Shellharbour, Kiama, Shoalhaven)	COORDINAIRE – the South Eastern New South Wales Primary Health Network	2
“Central Coast” (Gosford, Wyong)	Central Coast Local Health District	3
“Murrumbidgee” (Bland, Cootamundra, Griffith, Hay, Junee, Leeton, Tumut Shire, Wagga Wagga, Young)	Murrumbidgee Primary Health Network	4

### Randomization

After selecting the sites according to the inclusion criteria, the four sites (clusters) were randomized to a start order. Randomization was performed using the “sample” function in R, to generate a random order of numbers between 1 and 4 without replacement. Cluster randomization was undertaken for administrative convenience, and for the ecological validity of providing the intervention at the community level. Randomization was carried out by a statistician not involved in the day-to-day conduct of the trial according to ICH Guidelines.

### Study setting

The LifeSpan model is being delivered into the four distinct geographic regions in NSW described above (Newcastle, Illawarra Shoalhaven, Central Coast, and Murrumbidgee). Geographically defined outcome data were built up to the LGA level from a set of Australian Bureau of Statistics (ABS) 2016 State Suburbs Codes (SSCs). The ABS SSCs will be static for 5 years, meaning that regardless of the boundary variations associated with LGAs during the active trial phase, suicide incidents and delivery of the LifeSpan strategies will remain in-scope.

### Intervention

The LifeSpan intervention consists of nine evidence-based suicide prevention strategies. These strategies include universal strategies designed to reach the entire population (regardless of risk), selective strategies which target subgroups of the general population that are determined to be at risk for suicide and indicated strategies for individuals who are experiencing early signs of suicide crisis or behavior. The implementation of all nine strategies within each region over the 2 years of active intervention (Fig. 1) is managed by site coordinators in collaboration with the LifeSpan central team and relevant organizations or services, with the intention that all are operating simultaneously within a region by the end of Year 2. For some of the strategies, there are multiple programs or resources that are recommended and supported by LifeSpan funding. Trial sites will be required to implement at least one program or resource under each of the nine strategies. The nine interventions are described below, grouped according to universal, selective, and indicated strategies.

### Program components

#### Universal prevention strategies

Means’ restriction activities, informed by a detailed suicide profile for each region that identifies hotspots and priority meansTraining in best-practice Mindframe media reporting guidelines [11] for local journalists and key media representativesSchool-based suicide prevention programs delivered to all studentsPublic awareness raising of suicide and health promotion in partnership with *R U OK?* [12] and delivered during national suicide prevention awareness week

#### Selective prevention strategies

5.Suicide Prevention Gatekeeper training for the whole community, using the Question, Persuade, Refer (QPR) program [13].6.Training for frontline responders for upskilling in how to support individuals with suicidal ideation or self-harming behaviors7.Training in psychosocial treatments for suicide to psychologists and allied health professionals, and implementation of the Collaborative Assessment and Management of Suicidality (CAMS) [14] framework in relevant healthcare settings8.Capacity building and training in suicide detection for general practitioners (GPs) through face-to-face training programs, and digital tools to assist with early detection and referral

#### Indicated strategies

9.Establishment of aftercare services in sites where such services do not exist, to provide support to individuals following a suicide attempt, and development and dissemination of best practice guidelines for effective crisis and aftercare [15] for emergency departments (EDs)

See Appendix for a comprehensive description of the nine strategies.

### Control condition

As part of the stepped-wedge design, each site contributes pre-intervention or “control” data. Rates suicide attempts and suicide deaths and their temporal trends will be established based on at least a decade of data from 2012, acquired retrospectively, from archival coronial data, ambulance data, hospital separations and ED data. Data will be acquired at a unit (patient) level, with geocoordinates of incident location, so that suicide data can be mapped to each of the four sites.

### Outcomes

#### Primary outcome

The primary outcome of the study will be the rate of treated suicide attempts in the period from full implementation of LifeSpan until March 2020. This rate will be compared to rates and their temporal trend in the pre-intervention period (defined in each site as the period from July 2012 until the start of implementation). There is currently no gold standard dataset for suicide attempt; for this study we will identify self-harm attempts using three key datasets from the Centre for Health Record Linkage, NSW Health, which are outlined in Table 2. Incidents to be included in the linkage will be determined using International Classification of Diseases Australian Modification codes for intentional self-harm (i.e., X60-X84 (intentional self-harm), Y87.0 (sequelae of intentional self-harm)) [16]. Data will be obtained for the period of 2012–2021, where possible, and each incident case will geocoded to a specific incident address using longitude and latitude coordinates. The incident addresses will also be geocoded to a suburb using Australian Bureau of Statistics (ABS) 2016 State Suburb Codes (SSC) so that each case can be assigned to one of the four respective regions. By linking these three datasets, duplicate incidents will be able to be removed and the maximum number of self-harm cases identified. Narrative text fields in all datasets will be reviewed to maximize identification of suicide attempt cases. Waiver of consent is requested for all attempt and mortality data as data aggregation for outcome analyses means that there is a low or negligible risk that individuals will be identifiable.

**Table 2 Tab2:** Primary and secondary outcome data sources

	Suicide mortality data	Suicide attempt data		
	National Coronial Information System (NCIS)	NSW ambulance data	NSW Admitted Patient Data Collection (APDC)	Emergency Department Data Collection (EDDC)
**Level data to be acquired at**	Individual/point data	Individual/point data	Individual/point data per hospital separation	Individual/point data
**Years data will be acquired for**	Jan 2006 – Dec 2021	Jul 2012 – Jun 2021	Jan 2007 – Jun 2021	Jan 2007 – Jun 2021
**Summary of data**	The NCIS is a data-storage, retrieval, analysis, interpretation, and dissemination system for coronial information. It enables coroners, their staff, public sector agencies, researchers, and other agencies to access coronial data to inform death- and injury-prevention activities	Ambulance data contains a collection of operational information from computer-aided dispatch (CAD), electronic medical records (eMR), and data documented by clinicians through patient healthcare records	APDC records all inpatient separations (discharges, transfers, and deaths) from all public, private, psychiatric, and repatriation hospitals in New South Wales (NSW), as well as public multi-purpose services, private day-procedure centres, and public nursing homes	The EDDC is an administrative data collection detailing presentations to emergency departments at public metropolitan hospitals in NSW. Diagnosis coding is not by trained clinical information manager but by medical, nursing, or clerical personal

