#### Follow-up

Primary and secondary outcome data will be acquired for 12 months post baseline (end of Year 1 of active intervention) and 24 months post baseline (end of Year 2 of active intervention), though the primary point of interest is the latter.

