#### Sample size and statistical analysis

In the primary outcome analysis, changes in suicide attempt presentation rates per 100,000 population will be tested by comparing the mean annual attempt rate from July 2012 until the implementation date (pre-implementation) with the mean annual attempt rate from the implementation date till the end of the active implementation period (24 months post baseline), combined across all four trial sites. To determine whether the changes in trial-site suicide attempt rates were different to those occurring elsewhere, sensitivity analyses will use the suicide attempt rate for the rest of the NSW population as a background rate. Subsequent analysis will examine changes in treated suicide attempt rates pre and post implementation by individual site. The treated suicide attempt rate will be calculated per 100,000 population using the three linked datasets described for the primary outcome: ambulance data, ED data, and admitted patient data.

To examine changes in suicide deaths, the pre- and post-baseline rates per 100,000 will be calculated using data from the National Coronial Information System. As for the suicide attempt rates, the suicide death rates will be examined for all four trial sites collectively and for each individual site and compared with the background suicide death rates for the remainder of the NSW population in sensitivity analysis.

The alpha level will be set at 0.05 for all analyses.

The mean rate of treated suicide attempt presentations in the period 2005–2013 was approximately 250 per 100,000 per year in the four target sites, based only on hospital admission records. We have previously calculated that the nine strategies could, cumulatively or synergistically, reduce the rate of attempts by up to 30% [6]. However, the magnitude of the effect of a multilevel approach is likely to vary by the extent and length of implementation, the reach of exposure of individuals to multiple strategies, and the existing quality and availability of services and initiatives within communities at baseline. Detecting such change within one trial site relative to another trial site, with 90% power, would require a population within each site of at least 79,000 people. As each trial site has at least 145,000 population, we will be able to detect reductions of approximately 7% in suicide attempt rates within each site.

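### The primary-outcome window is defined in two ways that cannot both hold for all four sites

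*Protocol article*

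**What the plan says.** The protocol article describes the post-intervention period in several places.

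- **Outcomes, Primary outcome:** the outcome is "the rate of treated suicide attempts in the period from full implementation of LifeSpan until March 2020". The comparison period in each site runs from July 2012 to the start of implementation.
- **Sample size and statistical analysis:** the pre-implementation mean annual rate is compared "with the mean annual attempt rate from the implementation date till the end of the active implementation period (24 months post baseline"), combined across the four sites.
- **Follow-up:** data are taken at 12 months and at "24 months post baseline (end of Year 2 of active intervention), though the primary point of interest is the latter". The secondary outcomes also refer to 24 months.
- **Abstract, Methods:** "with evaluation extending a minimum of 24 months after establishment of the full active period".
- **Secondary hypotheses:** the comparison with the rest of the State is made "in the period after the full establishment of the program compared to the remainder of the State".

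Three statements bear on what these terms mean. Under Study design, sites cross over at 4-month steps. The same section says that sites are not regarded as fully exposed in the 6-month establishment phase, yet that this phase will be used in estimating the effect. On the active phase it says: "By the end of this 2-year period, all nine strategies are intended to be operating simultaneously". The Intervention section repeats that intention. *Full implementation* is not defined anywhere.

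**The concern.** A primary outcome needs one start and one end for its post period. Here the outcome definition has an undefined start and a calendar end shared by all sites, whereas the analysis section has a start and an end specific to each site.

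Two things are at stake. First, the windows contain different months and weight the sites differently. Table 2 plans attempt data to June 2021, so several windows will be computable, and an unresolved choice could be made after the rates are seen. Second, the estimand changes. A window over the first 24 active months averages the effect while strategies are still being introduced; a window that starts once all nine are running targets the complete model. The Discussion concedes that some strategies may be hard to implement within 2 years and that effects may be delayed, so the two could differ materially.

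**Working it through.** **1. Contradiction without dates.** Let site 1 become active in month *s*. With 4-month steps, site *k* starts at *s* + 4(*k* − 1), so site 4 starts 12 months after site 1.

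- Analysis-section window: ends at *s* + 4(*k* − 1) + 24, which is four different dates.
- Outcome-definition window: ends in March 2020 for every site.

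Four dates spaced 4 months apart can match one fixed date at most once. No meaning of *full implementation* removes this, because that term affects only the start.

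**2. Months in each window.** The readable text gives no site start dates, and Fig. 1 is not shown. I assume that site 1 was active from April 2017. This fits prospective registration on 28 March 2017, and it puts the end of site 4's 24 active months at March 2020. The starts are then April 2017, August 2017, December 2017 and April 2018.

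| Window | Site 1 | Site 2 | Site 3 | Site 4 | Site-months |
|---|---|---|---|---|---|
| Active start to 24 months | 24 | 24 | 24 | 24 | 96 |
| Active start to March 2020 | 36 | 32 | 28 | 24 | 120 |
| End of year 2 to March 2020 | 12 | 8 | 4 | 0 | 24 |

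The third row shares no month with the first, whatever the start date.

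**3. Sensitivity to the assumed start.** Randomization was in July 2016. If the 6-month establishment phase followed it, site 1 could not be active before about January 2017.

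| Site 1 active from | Active start to March 2020 | End of year 2 to March 2020 |
|---|---|---|
| January 2017 | 39/35/31/27 | 15/11/7/3 |
| February 2017 | 38/34/30/26 | 14/10/6/2 |
| March 2017 | 37/33/29/25 | 13/9/5/1 |
| April 2017 | 36/32/28/24 | 12/8/4/0 |
| July 2017 | 33/29/25/21 | 9/5/1/0 |

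On the end-of-year-2 reading, site 4 has between 0 and about 3 months.

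**4. The abstract's wording.** Read from active start, a minimum of 24 months fits 36/32/28/24. Read from the point when all nine strategies run, site 4 would need data to March 2022 (April 2018 plus 48 months), but attempt data are planned only to June 2021.

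**5. Illustration of what the choice can do.** The plan gives no figure for the windows. Its 79,000 per site does reproduce: 250 against 175 per 100,000, two-sided 0.05, 90% power, two-proportion formula without continuity correction, gives 79,219. The same rate is used below.

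Suppose the effect grows linearly from 0 to *R* over 24 months and then stays at *R*. The mean effect in each window is:

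- active start to 24 months: *R*/2
- active start to March 2020: (96 × 0.5 + 24 × 1)/120 × *R* = 0.6*R*
- end of year 2 to March 2020: *R*

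With *R* = 7%, these are 3.5%, 4.2% and 7%. If instead nothing happens in year 1 and growth is linear in year 2, the first window shows *R*/4 (30% becomes 7.5%).

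Approximate Poisson power is Φ(|ln RR|/√(1/E₀ + 1/E₁) − 1.96). Here E₀ = 4 × 145,000 × 5.25 years × 0.0025 = 7,612.5, where 5.25 years is the mean of 57, 61, 65 and 69 pre months. E₁ is the expected post count under the effect.

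| Window | Mean effect | E₁ | Power |
|---|---|---|---|
| Active start to 24 months | 3.5% | 2,900 × 0.965 = 2,798.5 | 36% |
| Active start to March 2020 | 4.2% | 3,625 × 0.958 = 3,472.75 | 55% |
| End of year 2 to March 2020 | 7% | 725 × 0.93 = 674.25 | 44% |

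A constant 7% over the first window would give 90%. None of these figures allows for clustering or trend.

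**The case against.** **Active start is arguably the natural meaning of *full implementation*.** Study design denies full exposure only to the establishment phase, which suggests that exposure counts as full from active start. The abstract's minimum of 24 months fits 36/32/28/24. The other reading would leave 24 months per site in neither comparison period, since the pre period stops at the start of implementation. This stands as an argument about meaning: end of year 2 is one possible reading and not an established fact. It does not remove the conflict, because the end dates still differ.

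**A reader might infer that site 4 contributes no post-intervention data.** The documents do not support that. The zero needs one particular reading and a start date that the readable text does not give. Even then, it means no data after all nine strategies are running; site 4 still has active-phase data.

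**A reader might also take unequal follow-up as a defect in itself.** It is not. A common calendar end after staggered starts is ordinary in a stepped-wedge design. The error is the mismatch with the analysis section.

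**The power figures are soft.** They use the minimum population for every site, a rate based only on hospital admissions, and an assumed ramp. The linked outcome also draws on ambulance and emergency data. At an assumed 375 or 500 per 100,000, the three powers become 51/73/60% or 63/84/72%. Some components also start early: media training is in year 1, and gatekeeper training is available throughout the active phase. This objection stands; the figures show only that the choice can matter.

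**Conclusion.** The concern holds as an inconsistency in the definition of the primary outcome. The outcome definition and the analysis section give post periods that can share an end date in at most one of four sites, and this follows from the text and the 4-month steps alone. The post period totals 96, 120 or 24 site-months according to reading, if site 1 became active in April 2017. The estimand moves with it, from an average over roll-out to the effect of the complete model. The documents do not settle which meaning of *full implementation* was intended, and the ramp and power results are illustrative. Because the protocol itself fixes the window twice and differently, this is not a detail that can be left to an analysis plan. It should be corrected before outcome data are analysed.

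**What to change.** Before outcome data are analysed:

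1. Define *full implementation*.
2. State one start and one end of the post period, and use them identically in the Abstract, Secondary hypotheses, Primary outcome, Secondary outcomes, Follow-up, and Sample size and statistical analysis. One workable choice is each site's active start to 24 months, which Follow-up and the analysis section already point to.
3. Reconcile the Study design statement on the establishment phase with that window, saying whether those 6 months count as control, as exposed, or as neither.
4. Report any other window (active start to March 2020, or after year 2 using the attempt data planned to June 2021) as a pre-stated secondary or sensitivity analysis. Separate exposure terms for year 1 and year 2 are optional.

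**Cost.** No new data are needed. The changes are to wording in several sections, but the trial is registered and this is its primary outcome, so the change should be dated, justified and checked against the registration. A 24-month window leaves the later months of the earlier sites out of the primary estimate (12 + 8 + 4 = 24 site-months to March 2020 under the April 2017 assumption) and averages over roll-out. The pre-stated secondary analysis addresses both.
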